##### Secondary Analyses

In order to investigate associations between parent satisfaction with FCC practices and parent, as well as infant outcomes, we will use multilevel models with PCICU as the level two factor. Such models account for shared exposure to unit characteristics, causing families within a unit to be more similar (to an unknown extent) compared to families from different units.

For the analysis of outcomes on the parent level, we will enter parent satisfaction with FCC as independent variable. Measures of parent well-being (specifically, symptoms of anxiety, depression, stress and parenting stress) will be entered as dependent variables. Extended models will be built to account for potential effects of infant characteristics (e.g., age and gender), medical variables (e.g., duration of stay at hospital, complexity of disease), as well as socio-demographic variables (e.g., employment status, ethnicity or professional background).

For each measure of parent well-being (symptoms of anxiety, depression, stress and parenting stress), a series of multilevel models is estimated. Each model in the set has incremental complexity. All models will be estimated using Restricted Maximum Likelihood, defining the covariance structure through variance components, and using the Huber- White sandwich estimator for the standard errors (50, 51).

For *each* parent well-being measure separately, the series of hypothesis confirming models is outlined below:

1) Model 1 estimates the unconditional means model for the parent well-being score.2) Model 2 estimates the conditional means model, adjusting for infant characteristics, medical and socio-demographic variables.3) Model 3 estimates the random intercept for the fixed slope association between FCC satisfaction and parent well-being, adjusted for infant characteristics, medical and socio-demographic characteristics.4) Model 4 estimates the random intercept and random slope for the association between FCC satisfaction and parent well-being, adjusted for infant characteristics, medical and socio-demographic characteristics.

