For the analysis of outcomes on the child level, we will enter parent satisfaction with FCC as independent variable. Measures of infant well-being (specifically, mental and physical well-being as rated by the parents) will be entered as dependent variables. Extended models will explore potential effects of infant characteristics (e.g., age and gender), medical variables (e.g., duration of stay at hospital, complexity of disease), as well as socio-demographic variables (e.g., employment status, ethnicity or professional background). Two series of models are estimated for child well-being (parent-rated physical and parent-rated mental well-being). Similar to above analysis, each model in the set has incremental complexity and all models will be estimated using Restricted Maximum Likelihood, defining the covariance structure through variance components, and using the Huber-White sandwich estimator for the standard errors.

For each child well-being measure separately, the series of hypothesis generating models is outlined below:

1) Model 1 estimates the unconditional means model for the child well-being2) Model 2 estimates the conditional means model, adjusting for infant characteristics, medical and socio-demographic variables.3) Model 3 estimates the random intercept for the fixed slope association between FCC satisfaction and child well-being, mutually adjusted and adjusted for infant characteristics, medical and socio-demographic variables.4) Model 4 estimates the random intercept and random slope for the association between FCC satisfaction and child well-being, adjusted for infant characteristics, medical and socio-demographic variables.

In all series of models, the change in model deviance between subsequently nested models is evaluated at a 5% significance level using the Likelihood Ratio Test.

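### The plan applies likelihood ratio tests to REML fits with different fixed effects, so the Model 2 to 3 test of FCC satisfaction depends on how the questionnaires are scored

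*Protocol article*

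**What the plan says.** The Secondary Analyses section of the protocol article sets out a four-step series for each outcome. For the parent outcomes it fixes the estimator: "All models will be estimated using Restricted Maximum Likelihood, defining the covariance structure through variance components", with Huber-White standard errors. The child series repeats that "all models will be estimated using Restricted Maximum Likelihood".

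The steps that matter are:

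- "Model 2 estimates the conditional means model, adjusting for infant characteristics, medical and socio-demographic variables".
- "Model 3 estimates the random intercept for the fixed slope association between FCC satisfaction and parent well-being", with the same adjustment.
- "Model 4 estimates the random intercept and random slope for the association between FCC satisfaction and parent well-being", again with the same adjustment.

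For the parent outcomes (anxiety, depression, stress, parenting stress), "the series of hypothesis confirming models is outlined below". The section closes with a rule for every series: "the change in model deviance between subsequently nested models is evaluated at a 5% significance level using the Likelihood Ratio Test".

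The Analysis Plan section names SPSS and R (with lmer) and does not say which program fits these models. The instrument descriptions give item counts and response ranges, but do not say whether EMPATHIC-30, the DASS-21 subscales or PSS:NICU enter as sums or item means.

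**The concern.** REML works with the part of the data left after the fixed effects are projected out. Two models with different fixed effects leave different parts, so their restricted likelihoods describe different data and the difference in deviance is not a likelihood ratio. Model 1 to 2 adds the covariates and Model 2 to 3 adds the FCC satisfaction slope, so both steps are affected. Model 3 to 4 keeps the same fixed effects and is not affected for this reason.

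Model 2 to 3 isolates the association that the parent hypotheses are about. If its deviance change is used to decide, the same data can be significant or not according to the scoring of the questionnaires. The power figures in the Power Analysis and Sample Size section would not describe that test.

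**Working it through.** **The plan's own figures.** With 140 families per centre and two-sided 5%, the noncentral t distribution (278 df) gives 80.9% power at d = 0.34; the minimum detectable d is about 0.335, stated as 0.34. The multilevel pair is consistent with itself: 0.34 × (1.960 + 0.842)/(1.960 + 0.643) = 0.366, stated as 0.37. The 74% cannot be rebuilt, because the simulated design is not described. These figures are not in dispute.

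**The scale shift (no assumed SDs needed).** With n observations and p fixed effects, the REML deviance in its usual form is

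(n − p) ln 2π + ln|V| + ln|X′V⁻¹X| + r′V⁻¹r.

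- Multiply the FCC score by k. Only Model 3 contains it, and there ln|X′V⁻¹X| rises by 2 ln k. The Model 2 minus Model 3 statistic falls by 2 ln k.
- Multiply the outcome by c. Each deviance rises by 2(n − p) ln c. Model 3 has one more fixed effect, so the statistic rises by 2 ln c.

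Item counts from the instrument descriptions give:

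| Scoring change | Shift in statistic |
|---|---|
| EMPATHIC-30 (30 items), mean to sum | −2 ln 30 = −6.80 |
| DASS-21 subscale (7 items), sum to mean | −2 ln 7 = −3.89 |
| PSS:NICU (13 items), sum to mean | −2 ln 13 = −5.13 |

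The 5% critical value for one added slope is 3.84; each shift exceeds it.

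Direct refits of simulated data matched these shifts to four decimals. One dataset with no true association gave, for predictor/outcome scored mean/sum, sum/sum, mean/mean and sum/mean, statistics of −0.45, −7.26, −4.35 and −11.15. The maximum likelihood (ML) statistic was 0.01 throughout. A valid likelihood ratio statistic cannot be negative.

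**Error rate and power.** Taken from the article: 2 × 140 families and an intraclass correlation of 0.40. Assumed: six covariates; SD 0.6 for the EMPATHIC-30 mean, 4 for a DASS-21 sum and 10 for a PSS:NICU sum; and a standardised slope of 0.17, chosen so that ML has about 80% power.

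The simulated rates can be checked by hand. Without covariates, the REML statistic is roughly z² + ln 2π − ln(n·s_x²/s_e²). For EMPATHIC mean and DASS sum, s_e² = 16 × 0.60 = 9.6, so n·s_x²/s_e² = 280 × 0.36/9.6 = 10.5. The offset is 1.84 − 2.35 = −0.51, and rejection needs z² > 3.84 + 0.51 = 4.35, which has null probability 3.7%. The other offsets follow from the shifts above, plus 2 ln 2.5 = 1.83 for the larger PSS:NICU SD.

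| EMPATHIC-30 / outcome | Offset | Type I, by hand | Type I, simulated | Power, simulated |
|---|---|---|---|---|
| mean / DASS sum | −0.51 | 3.7% | 3.7–4.2% | 76–77% |
| sum / DASS sum | −7.32 | 0.08% | 0.05–0.13% | 29–31% |
| mean / DASS mean | −4.41 | 0.4% | 0.4–0.5% | 47–49% |
| sum / DASS mean | −11.21 | 0.01% | 0% | 13–15% |
| both standardised | −4.31 | 0.4% | 0.4–0.5% | 47–49% |
| mean / PSS:NICU sum | +1.32 | 11.2% | 11.0% | 88% |
| sum / PSS:NICU sum | −5.48 | 0.2% | 0.2% | 41% |
| ML, any scoring | – | 5% | 5.3–6.0% | about 80% |

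Main scenarios used 4,000 to 6,000 datasets. A check of the DASS rows at intraclass correlation 0.05 (2,000 datasets) gave a similar pattern. Standardising both variables does not cure the problem. Doubling the DASS-21 score (assumed SD 8, EMPATHIC SD 0.7, eight covariates) gave 10.7% and 89%, but the article does not mention doubling, so that case is left out of the range reported here.

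**The case against.** **The likelihood ratio test may only be a model-building step.** The article does not say that the Model 2 to 3 comparison decides the hypothesis. Huber-White standard errors do not enter a likelihood ratio test; they serve tests or intervals for coefficients, and a coefficient test does not depend on scale. A reader might infer that the deviance test is the sole confirmatory rule. The text does not say so. What it does say is narrower: this is the only test in the series given a significance level, and no decision rule is attached to the coefficient.

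**R may refit by ML.** The only multilevel fitting tool named is lmer, and comparing such fits in R may trigger an ML refit by default. That would remove the problem in practice, so the eventual results need not be wrong. But the article prescribes REML for all models and also names SPSS. A confirmatory rule should not rest on an unstated default that contradicts the written method.

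**The error is not universal.** This stands. With EMPATHIC-30 as a mean and DASS-21 as a sum, error and power are close to nominal. Most of the other scorings tried are conservative; only one in the table inflates type I error. A reader might infer that the confirmatory tests can never have a 5% error rate or the planned power, and the figures do not support that.

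**The analyses are secondary.** This also stands. The primary ANCOVAs and the stated detectable effects are untouched, and the study claims no causal conclusions. But the parent series is the only part labelled confirmatory.

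**Conclusion.** The point holds for Models 1 to 2 and 2 to 3, in the parent and child series alike. As written, the plan pairs an estimator with a test that is not valid for it. This is a stated combination in the article, not detail left to a fuller document.

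The shifts of −6.80 and −3.89 against a critical value of 3.84 follow from algebra and the item counts alone. The rates (type I error about 0% to 11%, power about 13% to 88% where ML has about 80%) rest on assumed SDs, covariates and slope. They show the possible spread and do not predict this study's error rate.

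A reader might extend the point to Model 3 to 4. The documents do not support that: the fixed effects are the same there, so REML deviances are comparable. The variance being tested does lie on a boundary, but that is a separate question.

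**What to change.** In the Secondary Analyses section, state that Models 1 to 3 are fitted by maximum likelihood for deviance comparisons that differ in fixed effects, and that REML is kept for the final estimates. Alternatively, name the t or F test of the FCC satisfaction coefficient in Model 3 as the 5% test for each parent outcome. With only two units, a sandwich estimate clustered at unit level has its own problem, so the standard error behind that test should be named. It is also worth stating whether each questionnaire enters as a sum or an item mean, although the ML statistic does not depend on it.

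Model 3 to 4 should not be given a 50:50 mixture chi-square as part of this change. With two units, under simplifying assumptions (equal precision, uncorrelated components, known residual variance), the slope variance is estimated as zero with probability P(χ²₁ < 1) = 0.68 rather than 0.50, and the 2.71 cutoff would have size about 2%.

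The cost is one sentence in the plan, with no extra data and no change to the sample size.

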## Discussion

Family-centered care is a compelling framework for the care for children with physical illness. Both premature infants and children with CHD have a risk for brain immaturity and are therefore neurologically vulnerable for stressors early in life. A protective environment during hospitalization may improve the mental and physical well-being of those infants. Our primary aim is to inventory FCC practices at two PCICUs in Germany. Results will provide insight into current FCC practices, the parents' experiences of these practices, and potential changes that can be implemented at those centers to further improve FCC practices. Results may be applicable to other centers in Germany and Europe. Secondary aim of the study is investigating associations between parent satisfaction with FCC practices and mental well-being of the parents, as well as physical and mental well-being of the child. These results will inform us about associations between parent experiences with FCC and parent and infant outcomes in pediatric cardiology. They may provide the basis for international follow-up studies in this population, with more elaborate, longitudinal and experimental research designs, in order to advance insights into the benefits of FCC in this population.

As this study is conceptualized as cross-sectional, this study is time efficient. Filling out the questionnaires will take ~30 min in total. Implementation of the study will be closely monitored at both centers and time expenditure for medical stuff recruiting the families at the normal/intermediary ward is manageable. We therefore expect a high participation rate. Results will be representative for the population of primary caregivers with hospitalized infants with CHD. Due to the cross-sectional study design, no cause-and-effect relationship can be established between any of the variables. As part of the research questions are hypothesis generating, results will have to be replicated in hypothesis confirming research. Randomized clinical follow-up trials will be essential. Additionally, follow-up studies should ideally include qualitative research methodologies, such as interviews or focus groups, to provide rich data for an in-depth exploration of the topic (52).

Family-centered care potentially provides effective secondary prevention to medically vulnerable cohorts, particularly to children who are at risk for neurodevelopmental sequelae. Above that, the framework facilitates a value-based discourse about modern health care, putting theoretical paradigms like post-colonialism, critical feminism, relational inquiry and intersectionality on the agenda (53). It may therefore serve as counterbalance in increasingly economized systems, which exerts pressure on health care providers (54–57). Studying FCC in infants with CHD is an important step to optimize care for this population.

## Ethics Statement

The study was approved by the Ethics Committee at Charité Berlin (EA2/032/20) and the Ethics Committee at Ruhr-University Bochum (2020-713). Written informed consent to participate in this study will be provided by the participants' parents with custody rights. The study was registered in the German registry for clinical trials (Deutsches Register Klinischer Studien, www.drks.de) with registration number DRKS00023964.
